### Outcome measures

Participants will complete three study assessments: a baseline assessment and at 6 and 10weeks after the first session.

Primary outcome:
The intensity of pain: According to the VAS score, which will be evaluated in the first, sixth, and tenth sessions of the study. This quantitative and subjective variable consists of marking the degree of pain intensity in a straight horizontal line of a fixed length of 10cm. The ends are defined as the extreme limits of the parameter to be measured from left (worst) to right (best) [50, 51].

Secondary outcomes:
The quality of life related to health: Measured with the SF-12 Quality of Life health questionnaire. Specifically, the Spanish adaptation of the SF-12 Health Survey [52, 53] done by Alonso et al. [54, 55] will be used. The SF-12 is a reduced version of the SF-36 Health Questionnaire designed for cases in which a shorter questionnaire is required. While the SF-12 can be answered in an average of 2min, the SF-36 takes between 5 and 10min to complete. It consists of 12 items from the 8 dimensions of the SF-36 (physical function, social function, physical role, emotional role, mental health, vitality, body pain, and general health status). A higher score means better quality of life.The kinesiophobia: Fear of movement will be measured by the Tampa Scale for Kinesiophobia (TSK-11). This questionnaire, created by Miller et al. [56], quantifies the intensity of kinesiophobia suffered by the patient. The reduced version and adaptation to Spanish by Gmez-Prez et al. [57] will be used. It consists of 11 statements that the patient must answer using a Likert-type scale from 1 (totally disagree) to 4 (totally agree). A higher score means a greater degree of kinesiophobia.The catastrophizing: Measured with the Pain Catastrophizing Scale (PCS) [58]. This 13-item questionnaire assesses the patient's catastrophic thoughts using a five-point Likert scale. It consists of three subscales (rumination, magnification, and hopelessness). A higher score means a greater degree of catastrophizing. The Spanish adaptation validated by Garca Campayo et al. [59] will be used.Sociodemographic variables, pathological history, and clinical history: Assessed in the first treatment session and collected through a standardized clinical history.Adverse events: Recorded in each of the treatment sessions through patient references to his or her status and evolution.Adherence to treatment: Assessed in each of the treatment sessions and collected through a compliance form designed for the project.

### Schedule Table 3

**Table 3 Tab3:** The different schedule phases are shown in italics

	Recruitment	Session 1	Sessions 25	Session 6	Sessions 79	Session 10
**Recruitment:**						
Selection screening	X					
Informed consent	X					
Allocation	X					
**Interventions:**						
Intervention CG (deactivated CRMRF		X	X	X	X	X
Intervention IG (activated CRMRF)		X	X	X	X	X
**Evaluations:**						
Demographic variables		X				
Clinical variables		X				
VAS		X		X		X
SF-12		X		X		X
TSK-11		X		X		X
PCS		X		X		X
Compliance form		X	X	X	X	X
Recording of adverse events		X	X	X	X	X

### Sample size

To estimate the sample size, version 7.12 (April 2012) of the sample size calculator of the GRANMO program was used. This version can be obtained at the following link: https://www.imim.es/ofertadeserveis/software-public/granmo/.

For this estimate, alpha values of 5% and beta values of 20% (power of 80%) were taken into account. Based on data published in the literature [60] and applying a common standard deviation of 3 and a difference equal to or greater than 2 in the VAS, 40 patients are needed for each leg of the study, assuming a maximum percentage of follow-up losses/dropouts of 10%.

### Selection of the sample

The selection of the sample will be done by sampling consecutive cases from the RAPbarcelona clinic in Barcelona. Health professionals from other institutions will be contacted to increase referrals to the center and an advertising campaign will be carried out on social networks. In physiotherapist appointments, patients with CPPS will be referred to the principal investigator. The protocol will be clearly explained to each of the interested patients who meet the selection criteria, and patients will be asked to sign an informed consent if they choose to participate. Patients will then be allocated to one of the two study groups.

### Random allocation of groups

Once participants are included in the study, they will be identified by the number from their computerized medical record and will be ordered sequentially and consecutively from 1 to 80 according to the order of recruitment. To assign interventions, CRMRF team engineers will enter the randomized sequence corresponding to each number from 1 to 80 into the study software to designate the CG and IG participants. In order to keep the assigned study group hidden from the patient, the physiotherapist, and the main researcher, the following four indications will be taken into account: (1) No parameter will appear on the screen visible to the CRMRF team that indicates whether the equipment emits an electrical signal. (2) The current intensity parameter will be 2% for all participants to prevent the intervention group patients from perceiving any thermal effect. (3) The physiotherapists will apply the CRMRF by manipulating the equipment with the handle and never with the electrode to avoid any sensation. They will be trained before starting the study. (4) The sequence of randomization and allocation will be kept hidden at all times from all patients, professionals, and the main researcher until the statistical analysis once the intervention is completed.

### Collection, management, and data analysis

Data will be collected in a specific database coded for this study, which will only be available to the main researcher. The database and statistical analysis will be performed with IBM SPSS Statistics 24.0 software.

First, a descriptive analysis of the characteristics of the patients included in both study groups, as well as the outcome variables will be carried out. To do this, absolute and relative frequencies (percentages) will be estimated for qualitative variables, and mean or median and standard deviation or range, respectively, depending on the normality of the distribution, for quantitative variables. Then, the comparative analysis of the two treatment groups will be carried out using the Chi-square test for qualitative variables and the Students *t* test for quantitative variables. Additionally, different associations between diverse variables will be analyzed. To check for the efficacy of the study treatments, intention to treat (ITT) and by protocol (PP) analysis will be performed.

The comparison of results will be done by promptly estimating the differences of the mean values of the outcome variables with their corresponding 95% confidence intervals (95% CI) and standard deviation (SD). Additionally, the adjusted differences will be calculated following the indications of the CONSORT document [61].

All data will be systematically included in the statistical database and an analysis of the results will be carried out individually for each participant both in the middle of the treatment (fifth session) and at the end (tenth session) to evaluate the evolution. The trial will cease if significant worsening, absolute improvement (VAS = 0), or unknown serious adverse events occur. A full preliminary results analysis will be performed when one-third of the sample size has been reached and the final analysis will be performed once the last participant has completed the intervention.

In all cases, the level of statistical significance established will be the usual (5%); therefore, statistically significant differences will be considered when p values are less than 0.05.

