### Procedure

Patients who agree to participate in the study will receive CRMRF therapy for 30min once a week. The first session, lasting between 45 and 60min, will serve to inform the patient, obtain signed informed consent, resolve any doubts about the study or questionnaires, and explain the theory of pain and health education.

At baseline, participants will undergo an initial assessment where data on age, medical history, surgical history, and clinical data will be collected. According to criteria used in previous similar studies [41, 42] palpation of the abdominal, lumbosacral, and perineal region will be performed, followed by internal palpation using the index finger at the vaginal and/or anal level to palpate the pelvic floor muscles, connective tissue, and internal organs, and to localize pain. During the first visit, the visual analog scale (VAS) will be used to measure the intensity of pain, the health questionnaire Short Form 12 (SF-12) to assess the quality of life, the Tampa Scale for Kinesiophobia (TSK-11) to assess kinesiophobia, and the Pain Catastrophizing Scale (PCS) to assess catastrophism. The same tests will be re-evaluated after 6 and 10 sessions. Also, at each session, treatment adherence and possible adverse events of the therapy will be identified and recorded in a database designed for the project.

The most common adverse reaction to the application of CRMRF, particularly at the beginning of treatment, is an increase in pain in the area lasting approximately 2 to 3days, which can be controlled with the local application of heat and the use of oral analgesics. In rare cases, due to the local application of heat, dermal irritation could appear. In this case, topical treatments may be applied. If the dermal irritation persists in the next session (after 1 week), it will be noted on the patients record sheet and the intervention will cease until it is completely resolved.

A total of 10 treatment physiotherapy sessions will be held weekly (Table 1).

**Table 1 Tab1:** Treatment sessions

	Intervention group (IG)	Control group (CG)
Session 1	Review of the information sheet and signing of informed consent. Collection and recording of baseline data (age, sociodemographic data, clinical data, and medical and surgical history). Self-completion of tests (VAS, SF-12, TSK-11, and PCS).	

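### As scheduled and tested, the promised ITT analysis of pain risks becoming a complete-case comparison, because every VAS is tied to a treatment session

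*Protocol article*

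**What the plan says.** **Analysis label.** Collection, management, and data analysis: "To check for the efficacy of the study treatments, intention to treat (ITT) and by protocol (PP) analysis will be performed". Neither set is defined there.

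**Test.** The same section compares the groups with the "Chi-square test for qualitative variables and the Students *t* test for quantitative variables". It adds mean differences with 95% confidence intervals, and adjusted differences whose method is not given.

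**Collection by session.** The primary outcome is pain intensity, "According to the VAS score, which will be evaluated in the first, sixth, and tenth sessions of the study". Procedure says "The same tests will be re-evaluated after 6 and 10 sessions". Tables 1 and 3 put VAS, SF-12, TSK-11 and PCS at sessions 1, 6 and 10. Neither table shows an assessment outside a session.

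**Collection by calendar.** Outcome measures opens differently: "Participants will complete three study assessments: a baseline assessment and at 6 and 10weeks after the first session".

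**Expected loss.** Sample size: "40 patients are needed for each leg of the study, assuming a maximum percentage of follow-up losses/dropouts of 10" per cent.

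**The concern.** An ITT comparison needs the outcome of every randomised participant, or a stated way to proceed without it. Here the outcome is scheduled at visits that a person who has stopped treatment no longer makes. A t test on session-10 values uses only those who have one, so someone who leaves after session 6 contributes nothing to the final contrast despite a recorded mid-treatment VAS.

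If the arms lose different kinds of patients, the people compared are no longer the randomised groups, and the primary estimate can shift in either direction. An analysis plan can change the test, but it cannot recover a VAS that nobody asked for. The collection schedule is protocol content, and it is stated in this article.

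**Working it through.** **1. The plan's own figure.** Inputs from Sample size: alpha 5% (two-sided reproduces the figure), power 80%, SD 3, difference 2, losses 10%.

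- n per arm = 2 × (1.960 + 0.842)² × 3² / 2² = 35.3, rounded up to 36.
- 36 / 0.9 = 40, as stated.

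The design thus expects a final VAS from about 36 of 40 per arm. This is ordinary inflation for loss and does not say who enters the ITT set.

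**2. Session and week timing.** Sessions are weekly, so session 6 falls 5 weeks after session 1 and session 10 falls 9 weeks after it. The calendar sentence gives 6 and 10 weeks. Procedure also lets the intervention be interrupted for persistent skin irritation, which moves session count and calendar further apart. The article does not say which governs.

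**3. Bias by arithmetic.** Score VAS so that higher means more pain. Let d be the share lost in an arm, and g the mean final VAS of those lost minus those retained. Then

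bias of the observed difference (IG − CG) = −(d_IG × g_IG) + (d_CG × g_CG).

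The document gives neither d nor g by arm, so all values are assumptions.

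| Lost IG / CG | g IG / CG | Bias (cm) |
|---|---|---|
| 10% / 10% | 2 / 2 | −0.2 + 0.2 = 0 |
| 15% / 5% | 2 / 2 | −0.3 + 0.1 = −0.2 |
| 15% / 5% | 3 / 3 | −0.45 + 0.15 = −0.3 |
| 10% / 10% | 2 / −2 | −0.2 − 0.2 = −0.4 |
| 20% / 0% | 3 / – | −0.6 |

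With standard error 3 × √(2/36) = 0.707 and no true effect, the two-sided type I error is 1 − Φ(1.96 − |bias|/0.707) + Φ(−1.96 − |bias|/0.707). This gives 5.9% for a bias of 0.2, 7.1% for 0.3, 8.7% for 0.4 and 13.6% for 0.6.

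**4. Simulation.** Assumptions: 40 per arm; three normal VAS values with SD 3 and correlation 0.5 or 0.7; 8 of 80 lost, with chance of loss weighted by exp(±0.5 × centred session-6 VAS); 3,000 runs per scenario.

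- Loss after session 6, same pattern in both arms: bias within about 0.03 cm.
- Loss after session 6, pattern differing by arm (8 against 0, or 4 against 4 with opposite weights): bias about 0.36–0.56 cm, null rejection about 9–13%.
- Loss after session 6, differing pattern working against the active arm, true difference 2 cm: bias of about the same size, power about 55–63%.
- Estimate using baseline and session-6 VAS when loss follows session 6: bias within about 0.03 cm. The simulated loss depends only on observed values, so this result is expected by construction.
- Loss before session 6 (8 against 0), so that only baseline is available: unadjusted bias about 0.35–0.51 cm. Adjustment for baseline still leaves about 0.15–0.21 cm.

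**5. Cost in power.** If 10% stop treatment and gain nothing, the expected difference is 0.9 × 2 = 1.8 cm. Non-central t power with SD 3 is 75.5% with all 40 per arm observed, and 70.9% with 36.

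**The case against.** The strongest case is that the article prescribes no complete-case analysis. Its calendar sentence, "Participants will complete three study assessments: a baseline assessment and at 6 and 10weeks after the first session", can be read as covering people off treatment. No sentence forbids assessing them and none rules out imputation. The adjusted differences could be more than a t test. The ITT set and missing-data rules are commonly left to an analysis plan or full protocol, which are not shown. All of this stands, and their absence is not the point here.

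Three stronger readings are tempting and are not supported:

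- **That the ITT result is a completers' result.** The documents support only a risk, which arises if the schedule and the named test are followed as written.
- **That the sample size section confirms that dropouts leave the analysis.** Dividing 36 by 0.9 is routine. "Losses" there can simply mean no final VAS.
- **That the early reaction will cause unequal loss.** Procedure says "The most common adverse reaction to the application of CRMRF, particularly at the beginning of treatment, is an increase in pain", but describes it as lasting about 2 to 3 days and controllable, and does not link it to withdrawal. The sham is visually identical, the setting is athermic, and allocation is concealed from patient and therapist. All of this makes arm-specific leaving less likely.

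It is also fair that the 8-against-0 pattern is a stress case: 20% in one arm, although 10% overall. And a model alone does not remove bias from loss before session 6. That limits the modelling remedy and strengthens the case for collecting the outcome.

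The mismatch itself is not answered. The article fixes session-based collection in its text and both tables, contradicts it once with calendar timing, and names ITT for the efficacy analysis.

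**Conclusion.** The point holds as a risk built into the stated schedule and test, and it is worth correcting. Followed as scheduled and tested, a participant who stops attending has no final VAS and leaves the session-10 comparison, even with a session-6 value.

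The bias is zero if the arms lose similar patients. With 10% lost overall and a pattern that differs by arm, it is about 0.4–0.5 cm, or 20–25% of the 2 cm target, with type I error about 9–13%. The direction cannot be predicted. These figures rest on assumed loss patterns, correlations of 0.5–0.7 and SD 3; only the SD, the 2 cm and the 10% come from the document. Confidence is medium, because an unshown plan may already handle missing values.

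**What to change.** 1. **Collection (main remedy).** In Procedure, Outcome measures and Table 3, reconcile session and week timing. State that VAS, SF-12, TSK-11 and PCS are sought at the scheduled mid and final dates from every randomised participant, whether or not still attending, remotely if needed. This comes first because a model cannot fully correct loss before session 6.
2. **Analysis.** In Collection, management, and data analysis, analyse all randomised participants in their allocated arm. Take the primary final VAS difference from a likelihood-based repeated-measures model of both post-baseline VAS values (arm, time, arm by time) including baseline VAS, so that session-6 values of late leavers contribute. The per-protocol analysis is supportive.

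**Cost.** Wording changes and a few remote questionnaires; the tests are self-completed. The sample size stays at 40 per arm. The effect estimated becomes that of offering CRMRF. If 10% stop and gain nothing, unadjusted t-test power for the resulting 1.8 cm is about 75% with 40 per arm observed and about 71% with 36.

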### Design

This manuscript describes a research protocol for a triple-blind, randomized controlled clinical trial. Participants will be equally (1:1) and randomly allocated into either an activated capacitive resistive monopolar radiofrequency group (intervention group, IG) or a deactivated capacitive resistive monopolar radiofrequency group (control group, CG). Both groups will receive pain education and physiotherapeutic techniques (myofascial therapy, trigger point therapy, and/or manual therapy). Participants, the investigators performing the intervention, and the statistical analyses will be blinded.

An analysis of the results will be carried out at 6 and 10weeks of treatment.

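### Adjustment for baseline VAS is not assured: the only named test is an unadjusted t test, and the planned adjusted differences have no covariate, model or rank

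*Protocol article*

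**What the plan says.** All references are to the Protocol article.

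- **Baseline is measured.** Procedure: "During the first visit, the visual analog scale (VAS) will be used to measure the intensity of pain". Outcome measures, on the primary outcome: "According to the VAS score, which will be evaluated in the first, sixth, and tenth sessions of the study". The schedule in Table 3 agrees, and SF-12, TSK-11 and PCS follow the same three-visit pattern.
- **The comparison.** Collection, management, and data analysis assigns the chi-square test to qualitative variables and the Student t test to quantitative ones. On the effect estimate it says: "The comparison of results will be done by promptly estimating the differences of the mean values of the outcome variables", with 95% confidence intervals.
- **Adjustment.** The following sentence reads: "Additionally, the adjusted differences will be calculated following the indications of the CONSORT document". It names no covariate and no model, and the section does not rank the adjusted and unadjusted estimates.
- **Sample size.** The inputs are "alpha values of 5% and beta values of 20% (power of 80%) were taken into account" and "applying a common standard deviation of 3 and a difference equal to or greater than 2 in the VAS". The calculation has no term for correlation with baseline.

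**The concern.** Earlier pain is usually a good predictor of later pain, so baseline VAS is the natural covariate for the primary outcome. The article schedules it for everyone but gives it no stated place in the comparison. Two things are at stake.

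1. **Precision.** An unadjusted comparison leaves in the error term all the outcome variation that baseline could explain. The interval is then wider than the same patients could support. Eligibility sets no minimum pain level and admits several aetiologies and both sexes, so baseline pain may well be spread out. That is an inference, because no baseline SD is given.
2. **An open choice.** An unadjusted and an adjusted estimate are both planned, significance is set at 5% throughout, and neither is named as the one that decides the trial. If they fall on opposite sides of 0.05, the text does not say which counts. The covariates could also be chosen after the data are seen.

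**Working it through.** **Inputs from the document:** difference 2, SD 3, alpha 5% (taken as two-sided), power 80%, loss 10%, 1:1 allocation (Sample size; Design).

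**Assumed:** the correlation r between baseline and follow-up VAS. It is not given, so 0.3, 0.5 and 0.7 are shown.

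**Step 1: reproduce the planned size.**
n per arm = 2 × (1.960 + 0.842)² × 3² / 2² = 35.3, rounded up to 36. Allowing for 10% loss, 36 / 0.90 = 40. This matches the stated 40 per arm. A one-sided test would give 28, or 32 after loss, and does not match. The stated size therefore fits a two-sided, unadjusted comparison of two means.

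**Step 2: the unadjusted test with 36 evaluable per arm.**
SE = 3 × √(2/36) = 0.707. The 95% CI half-width is 1.994 × 0.707 = 1.41. Power for a 2-point difference from the noncentral t is 79.7% (80.7% by the normal approximation). The test has the power the plan asks of it.

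**Step 3: the same patients with baseline VAS as covariate.**
Residual SD = 3 × √(1 − r²); SE = residual SD × √(2/36); half-width = t quantile × SE (about 1.99).

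| Assumed r | Residual SD | SE | CI half-width | Power for 2 points |
|---|---|---|---|---|
| 0 (unadjusted) | 3.00 | 0.707 | 1.41 | 80% |
| 0.3 | 2.86 | 0.675 | 1.35 | 83% |
| 0.5 | 2.60 | 0.612 | 1.22 | 90% |
| 0.7 | 2.14 | 0.505 | 1.01 | 97% |

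The interval narrows by 1 − √(1 − r²): about 5%, 13% and 29%.

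**Step 4: chance imbalance.**
If the baseline SD is also about 3 (assumption), the SE of the baseline difference is 3 × √(2/40) = 0.67 with all 40 per arm. A gap above 1 point in either direction then has a probability of about 14%. With 36 per arm the SE is 0.71 and the probability about 16%. With equal SDs, a baseline gap shifts the unadjusted outcome difference by about r times the gap. A 1-point gap therefore shifts it by about 0.3, 0.5 or 0.7 points, against a target of 2.

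**The case against.** The case on the other side has four parts.

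- **Adjustment is already planned, and this is an article.** The commitment to adjusted differences is explicit, and an analysis plan that is not shown may list the covariates. A reader might infer from the t test alone that adjustment has been abandoned; the text does not support that. What stands is that the article does make a choice: one named test, a sample size built on it, and adjustment only as an addition. Recommending the more efficient comparison as primary is more than asking for missing detail.
- **Nothing is invalid.** Under randomisation the unadjusted difference is unbiased, its standard error already allows for chance imbalance, and the sample size is right. All of this stands. It limits the point to precision and to the open choice of estimate.
- **The gain may be small.** At r = 0.3, power rises by only 3 to 4 percentage points and the half-width falls by 0.06. This also stands, since the document does not give r.
- **Stronger readings go too far.** A reader might infer that a baseline gap of about 1.4 points, the edge of the 95% range with 36 per arm, biases the result by 1.4. The expected shift is r times that, about 0.4, 0.7 or 1.0 points. A reader might also infer that a t test at one visit turns the intention-to-treat result into a completer result. The article plans intention-to-treat and per-protocol analyses separately and is silent on missing values, so that conclusion cannot be drawn from it.

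**Conclusion.** The point holds as a free improvement, not as an error. Adjustment for baseline VAS is not assured, and the article does not say which estimate decides the trial. The planned unadjusted comparison is valid and reaches about 80% power on the stated inputs. A primary analysis adjusted for baseline would reach about 83% to 97% with the same 36 evaluable per arm, and its 95% interval would be about 5% to 29% narrower. Those ranges rest on an assumed correlation of 0.3 to 0.7 and on the stated SD of 3 applying to follow-up VAS. The imbalance figures also need the assumption of a similar SD at baseline. The need to rank the two estimates depends on none of these assumptions.

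**What to change.** Before unblinding, name one baseline-adjusted comparison of session-10 VAS as the primary analysis. Either of these would serve:

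- an ANCOVA of session-10 VAS on group with baseline VAS as covariate; or
- a mixed model for sessions 6 and 10 with baseline VAS, group, visit and group-by-visit, with the session-10 group contrast as primary. This model also uses participants who have only one follow-up VAS.

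Use the same model for SF-12, TSK-11 and PCS, each with its own baseline score. Keep the t test as a sensitivity analysis and state that it does not decide the trial. The article also plans a preliminary analysis at one third of the sample, so record whether the choice was fixed before or after any results by group were seen.

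The cost is a few lines of wording in the protocol or analysis plan. No new data, visits or patients are needed, the sample size can stay as it is, and the SPSS software already named can fit both models.

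### A full analysis at one-third of the sample is planned at p<0.05 with no adjustment: the overall type I error is about 8.8% if a significant result at either look may count as efficacy

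*Protocol article*

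**What the plan says.** Four parts of the protocol article bear on this.

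- **Collection, management, and data analysis** plans two results analyses over the whole trial: "A full preliminary results analysis will be performed when one-third of the sample size has been reached", and then "the final analysis will be performed once the last participant has completed the intervention". The same section names Student's t test for quantitative variables and refers to intention-to-treat and per-protocol analyses of efficacy.
- **The closing paragraph of that section** sets one threshold: "In all cases, the level of statistical significance established will be the usual (5"%), that is, p below 0.05.
- **Sample size** uses one error rate: "alpha values of 5% and beta values of 20% (power of 80%) were taken into account". It makes no allowance for an earlier look.
- **Random allocation of groups**, item 4, keeps the sequence and allocation concealed from patients, professionals and the main researcher until the statistical analysis that follows completion of the intervention. **Design** adds that the statistical analyses are blinded.

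Nothing says what the one-third analysis is for, who sees it, whether it compares the arms, or whether a result from it could be claimed.

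**The concern.** An analysis described as full, in a section built around between-group tests, would ordinarily include the primary VAS comparison. A rule that applies 5% in all cases then covers that comparison at one-third of the sample and again at the end. Two chances to cross an unadjusted 0.05 threshold give more than a 5% chance of a false positive.

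This is not detail left for an analysis plan to supply, because the article states a threshold. A later plan that set a stricter interim level would have to depart from the published text.

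Two things are at stake. The first is the error rate behind the superiority claim. The second is the blind: pain on a VAS is subjective and self-reported, so knowledge of an early between-group result could influence the remaining two-thirds of the trial.

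**Working it through.** **Inputs from the documents**

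- Alpha 5%, power 80% (Sample size). Sidedness is not stated.
- "applying a common standard deviation of 3 and a difference equal to or greater than 2 in the VAS" (Sample size).
- "40 patients are needed for each leg of the study", "assuming a maximum percentage of follow-up losses/dropouts of 10"% (Sample size).
- Equal allocation: "Participants will be equally (1:1) and randomly allocated" (Design).
- Looks at one-third of the sample and at the end, each at p<0.05 (Collection, management, and data analysis).

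**Step 1: reproduce the planned sample size.** With a two-sided test, n per arm = 2 × (1.960 + 0.842)² × 3² / 2² = 35.3, rounded up to 36. Allowing for dropout, 36 / 0.90 = 40. This matches the plan. A one-sided 5% test gives 28 per arm before dropout, or 28 / 0.90 = 31.1, which does not match. I therefore take the test as two-sided, used once.

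**Step 2: type I error of two unadjusted looks.** Under the null, the test statistics Z1 (one-third) and Z2 (final) are approximately bivariate normal with correlation √(1/3) = 0.577, because the final data include the interim data. The chance of significance at one look or the other is

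1 − P(|Z1| < 1.96 and |Z2| < 1.96) = 0.0883, about 8.8%.

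| Information at first look | Overall type I error |
|---|---|
| 0.25 | 9.07% |
| 26/80 | 8.86% |
| 1/3 | 8.83% |
| 27/80 | 8.82% |
| 0.40 | 8.63% |
| 0.50 | 8.31% |

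The wider range matters because the text does not say whether one-third means recruited or completed. Simulated Student's t tests (200,000 replicates each) give 8.9% for 13 then 40 per arm, 8.7% for 14 then 40, and 8.9% for 12 then 36. Treating the looks as independent would give 1 − 0.95² = 9.75%, which is too high because they share data.

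**Step 3: the alternative case.** If no claim or stop can follow from the first look, only P(|Z2| ≥ 1.96) = 5% counts.

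**Step 4: how informative the early look would be.** One-third of 80 is about 27, so take 13 evaluable patients per arm (an assumption). With SD 3 and a true difference of 2:

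- Power of the t test is 37%.
- The 95% confidence interval half-width is 2.064 × 3 × √(2/13) = 2.43 points, wider than the target difference of 2.
- Among simulated trials that are significant at this look, the mean estimated difference is 3.15 points, so an early claim would tend to overstate the effect.

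**Step 5: boundaries that hold 5% overall (looks at 1/3 and 1).**

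| Rule | Interim p | Final p |
|---|---|---|
| O'Brien-Fleming type | 0.0007 | 0.0497 |
| Haybittle-Peto | 0.001 | 0.0495 |
| Pocock type | 0.0277 | 0.0277 |

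Moving the final test from 0.05 to 0.0497 lowers its t-test power from 83.76% to 83.69% at 40 per arm, and from 79.66% to 79.58% at 36 per arm. Both losses are below 0.1 percentage point.

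**The case against.** The strongest reply is that 8.8% is conditional. The protocol contains no p-value stopping rule and does not say that an interim result would be declared. If the trial runs on regardless and is judged on the final test, the error rate is 5%. That stands, and the point is worded accordingly.

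A second reply is that the phrase about all cases may mean all variables and tests rather than all time points, and that the blinding provisions leave room for a pooled, arm-blind look. This is a possible reading, but not a stated one. Coded arms could still be compared, and an analysis called full suggests more than pooled summaries. If a pooled look is intended, one sentence would settle the matter.

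A reader might go further and infer that this look can end the trial for efficacy, because the same paragraph says when the trial will cease. The text does not support that. The sentence directly follows one on analysing each participant individually and comes before the one-third analysis. Its triggers (worsening, VAS of 0, unknown serious adverse events) are clinical, and none is a between-group p value. The point does not rely on it.

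The figures for 13 per arm matter only if the early look is used for a claim.

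**Conclusion.** The plan is wrong as written, with a conditional consequence. It applies an unadjusted 5% level to a full early analysis and to the final one, and does not restrict the use of the first. The primary comparison then carries a two-sided type I error of about 8.8% if significance at either look may count as efficacy, and 5% if only the final test counts. To state flatly that the trial's false-positive rate is 8.8% would go beyond the text.

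The figure assumes two-sided testing (inferred from the reproduced sample size), one endpoint at one time point, and about one-third of the information at the first look. It does not cover the several outcomes, the two follow-up assessments, or the pair of intention-to-treat and per-protocol analyses.

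Separately, a comparative analysis partway through is not reconciled with concealing allocation until the intervention is completed. The article also makes the database available only to the main researcher, who is among those to be kept blind, and gives no route by which someone else would carry out the look.

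**What to change.** **Preferred.** State that the one-third analysis is limited to safety, adherence and pooled, arm-blind data, with no between-group efficacy test. The final test stays at 0.05, and the conflict with allocation concealment disappears. This costs no power.

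**If a comparative look is kept.** Have it done by someone independent of the blinded team, name who may see the result, and set an O'Brien-Fleming-type boundary: interim p<0.0007, final p<0.0497. Amend the sentence that applies 5% in all cases to match. Define one-third as participants with completed primary-outcome data, and recompute the boundary if the actual fraction differs.

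**If the look has already happened.** The Trial status section reports that recruitment began in April 2019, and this version is dated January 2021, so it may have. A boundary could then no longer be prospective. Report what was tested and who saw it, and base the efficacy conclusion on the final analysis only.

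The cost is a few sentences of wording, no extra patients, and at most a power loss under 0.1 percentage point.
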